#### Methods for handling protocol non-adherence and statistical methods for handling missing data {20c}

The research team will undertake all measures to minimize missing of data, and reasons for missing data, if any, will be ascertained using sensitivity analyses. Likelihood-based methods will be used if these reasons are rational. If the data are found to not miss at random, selection models and pattern-mixture models will be used. The *intent-to-treat* analysis will be used to evaluate our objectives based on the groups to which the participants are originally assigned after data transformation was performed.

#### Adverse event reporting and harms {22}

Therapeutic safety will be monitored on the basis of patient symptoms. Changes in pain, CPM, muscle soreness, and lumbar function degradation will be meticulously documented in the case report form.

#### Frequency and plans for auditing trial conduct {23}

We intend to conduct an audit every 6 weeks to examine all parts of research processes including participant enrolment, consent, eligibility, and allocation to study groups, as well as adherence to trial interventions, reporting of harms, accuracy, and ensuring timeliness of data collection.

#### Dissemination plans {31a}

The study results will be published in peer-reviewed indexed journals and distributed to the participants, healthcare professionals, the general public, and other relevant parties.

#### Publication {31b}

The results will be published irrespective of the outcome. Authorship shall be determined in accordance with the International Committee of Medical Journal Editors’ criteria. The authors have no limits on publication.

## Discussion

Although physical exercises have been considered as the foundation of management of musculoskeletal pain conditions with proven benefits [63], the precise mechanisms underlying the effects remain unclear [64]. Traditional explanations based on biomechanics and corresponding changes in loading of the musculoskeletal system regarding why exercise improves pain and disability in chronic musculoskeletal pain fail to consider the complete biopsychosocial spectrum of factors [65]. Exercise prescription is usually based on the preferences and expertise of the individual clinician. Because exercise prescription directly impacts intervention outcomes, analyzing the exercise parameters in patients along the chronic pain spectrum is crucial.

The study will offer the following benefits. First, it will help in acquiring more information and evidence about exercise-induced analgesia from the CPM perspective. Second, investigating the relationship between executive functions, CPM, and QoL will provide further inputs for high-quality randomized controlled trials in the future. Third, measuring the outcomes of exercises will help in scientifically prescribing different exercise types. The study outcomes will also help in identifying the characteristics of individuals responding or responding indifferently to exercises; this will avoid wastage of health resources or assist in directing the non-responsive individuals to other alternative interventions.

### Study strengths

The study intends to investigate only those outcome measures that have good psychometric properties, have been used extensively in research, and can be measured quickly. We will only recruit participants aged between 18 and 59 years as a previous study has hinted at a decline in endogenous pain modulatory and CPM functions with advancing age [66]. Studying the association between executive functioning, CPM, and exercises will be a major addition to the results as a previous study has indicated that this relationship is selectively sensitive and the positive effect observed on animals do not translate in humans [67]. Further, we will apply the optimal exercise dose in each group based on the methodology used in previous works.

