### Trial design {8}

This is a randomized, controlled, double-blinded study determining how CPM changes in response to three types of active exercises in CS-positive CLBP patients. Participants will be randomized to undergo 12 weeks of the motor control exercise (MCE), superficial strengthening (SS), or AE combined with patient education or patient education alone. This active treatment concurrent control design will be used to demonstrate superiority of one exercise group over another. All patients will be allocated in a 1:1:1:1 ratio using random number tables. All participants will receive advice to stay active. Another no-pain control group will also be recruited. The intervention will be provided for 12 weeks. An independent assessor will collect data at baseline (t0), after intervention at 3 months (t1), and at the 6-month follow-up (t2). Outcome measures include CPT for measuring CPM, letter–number sequencing subtest in the Wechsler Adult Intelligence Scale-III Edition (WAIS-III), Stroop neurophysiological test, QoL assessed using the abbreviated WHOQOL-BREF questionnaire, isometric muscle strength of spine and hip muscles, the Oswestry Disability Index (ODI) questionnaire, and the Numerical Pain Rating Scale (NPRS). Table 1 and Fig. 1 present the study design and flowchart, respectively. The research ethics approval was granted by the Integral University, India (IIAHSR/DO/PT/2022/23), and Composite Regional Centre for Skill Development, Rehabilitation, and Empowerment of Persons with Disabilities, India (CRCL/Ph.D. Data Collection/2021–22/1556). The study is designed according to the Consolidated Standards of Reporting Trials (CONSORT) guidelines and reported according to the Standard Protocol Items: Recommendations for Interventional Trials (SPIRIT) checklist. The study will use a 5 (between subjects − type of exercise interventions: MCE vs. AE vs. SS vs. patient education vs. no-pain control) × 3 (within subjects − time: before vs. after vs. 3 months after the intervention) mixed design.

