### Assignment of interventions: allocation

#### Sequence generation {16a}

Random number tables will be used to assign treatments.

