### Statistical methods

#### Statistical methods for primary and secondary outcomes {20a,b}

The Shapiro–Wilk test will be used to assess the normality of the distribution of the data. A one-way analysis of variance (ANOVA) will be used to compare baseline characteristics between the groups. Descriptive statistics will be used to calculate the mean values of all outcome variables collected. A repeated measure ANOVA statistic will be used to evaluate the effect of three types of exercise interventions on CPM, neurophysiological outcomes, pain, disability, strength measures, and QoL. The study will use a 5 (between subjects – type of exercise interventions: AE vs. MCE vs. SS vs. patient education vs. no-pain control) × 3 (within subjects – time: before vs. after vs. 3 months after the intervention) mixed design. Tukey’s post hoc analysis will be conducted to establish differences between the groups. Effect size will be estimated by dividing the mean difference in outcomes between the intervention and control groups by the combined standard deviation of the two groups [56].

The primary outcome will undergo a per-protocol analysis. Pearson correlation analysis will be performed to determine the relationship between patient characteristics (Table 4), CPM, executive functioning, pain, strength measures, disability, and QoL. Multiple linear regression analysis will be used to deduce the characteristics of individuals responding positively to exercise interventions. For all measurements, *p* will be considered significant, if it is < 0.05. The data collected will be analyzed using SPSS (Statistical Program for the Social Sciences) 16.0 (IBM Corp., Armonk, NY).

**Table 4 Tab4:** Summary of patient characteristics to be collected

Characteristics	CLBP group	Control group
Age (years)	X	X
Gender (male/female)	X	X
Pain episode duration (weeks)	X	X
Body mass index (kg/m^2^)	X	X
Education level (yes/no; school incomplete, completed secondary school, completed diploma/completed bachelors and above)	X	X
Employment status (yes/no; employed (full or part-time), unemployed, retired)	X	X
Marital status (yes/no; married/separated/ divorced, single)	X	X
Personal behaviors Alcohol status (yes/no) Smoking status (yes/no)	X	X
Comorbidities	X	X
Fear avoidance behavior	X	X
Perception of improvement	X	X

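### Age is a stated reason for the 18–59 entry limit and is collected, but the randomised CPM comparison does not use it: a modest, avoidable loss of precision

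*Protocol article*

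**What the plan says.** Study strengths explains the age limit. The protocol states "We will only recruit participants aged between 18 and 59 years" and gives as the reason that "a previous study has hinted at a decline in endogenous pain modulatory and CPM functions with advancing age".

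Table 4, in the statistical methods section {20a,b}, lists age among the characteristics collected in both the back-pain and the control groups. On the analysis, the same section says "A repeated measure ANOVA statistic will be used to evaluate the effect of three types of exercise interventions on CPM" and on the other outcomes. The design has five groups and three time points; the time factor is described as "within subjects – time: before vs. after vs. 3 months after the intervention) mixed design". Tukey comparisons between groups follow. No covariate is named.

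On allocation, Trial design {8} says "All patients will be allocated in a 1:1:1:1 ratio using random number tables", and Sequence generation {16a} says "Random number tables will be used to assign treatments". Neither mentions stratification by age.

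Age does have other uses in the plan: "A one-way analysis of variance (ANOVA) will be used to compare baseline characteristics between the groups", and "Pearson correlation analysis will be performed to determine the relationship between patient characteristics (Table 4), CPM" and the other outcomes. A multiple regression on the characteristics of responders is also planned. Study limitations says that confounders such as gender, body mass index and physical activity will not be considered; age is not in that list.

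**The concern.** The protocol treats a possible link between age and CPM as reason enough to restrict who may enter. The admitted range still spans 59 − 18 = 41 years. If CPM does vary with age inside that range, part of the between-person spread in CPM is explained by a variable the trial already holds. A model with only group and time leaves that part in the between-subject error. Comparisons of CPM means between arms are then somewhat less precise than the data allow. At stake is precision in the primary exercise-versus-exercise comparison, not its validity.

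**Working it through.** **Inputs.** From Sample size {14}: SD 100 kPa, difference 80 kPa, two-sided alpha 0.05, 30 per group, 87% power, 30% dropout, 43 recruited per group. Assumed, because the documents give no figure: a within-arm correlation r between age and CPM of 0.1 to 0.4.

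**1. The plan's own figures.**
- Standard error of a difference: 100 × √(2/30) = 25.8 kPa.
- Normal approximation: Φ(80/25.8 − 1.96) = 87.3%.
- Noncentral t, 58 degrees of freedom: 86.1%.
- Recruitment: 30/0.70 = 42.9, rounded up to 43.

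Both power values agree with the stated 87% to within a percentage point, and 43 per group is correct. Neither depends on adjusting for age.

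**2. Effect of adjusting for age.** The residual SD becomes 100 × √(1 − r²). Put back into the same calculation at 30 per arm (ignoring the one degree of freedom spent on age):

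| Assumed r | Variance removed (r²) | Residual SD (kPa) | Power, normal | Power, t | n per arm for 86.1% t power |
|---|---|---|---|---|---|
| 0 | 0% | 100.0 | 87.3% | 86.1% | 30 |
| 0.1 | 1% | 99.5 | 87.6% | 86.5% | 30 |
| 0.2 | 4% | 98.0 | 88.5% | 87.5% | 29 |
| 0.3 | 9% | 95.4 | 90.1% | 89.1% | 28 |
| 0.4 | 16% | 91.7 | 92.2% | 91.4% | 26 |

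On the t scale the gain runs from 0.4 to 5.3 percentage points, or from none to four patients per arm.

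**3. Which contrasts gain.** Write CPM for person i at time t as a group-by-time mean, plus b × age, plus person and error terms.
- *CPM at one time, or averaged over times:* b × age remains, so adjustment removes its variance. Tukey comparisons of group means across time are of this kind.
- *Change from baseline:* the term is b × age − b × age = 0. An age effect on CPM level that is constant over time cancels. Adjustment helps here only if age also affects how much CPM changes.

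Baseline is one of the three time points, so the group-by-time term is of the second kind. The power gains in step 2 belong to the first kind.

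**4. Chance age gaps.** At 30 per arm, an age difference between two arms at its 95% limit would shift a single-time CPM contrast by r × 100 × 1.96 × √(2/30) = 50.6r kPa: about 5 kPa at r = 0.1, 15 kPa at r = 0.3 and 20 kPa at r = 0.4. The variance of this shift is r² × 100² × 2/30, which is a fraction r² of the unadjusted variance 100² × 2/30. It is therefore already inside the 25.8 kPa standard error.

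**The case against.** The best case against the point is that nothing here is an error. Leaving a prognostic variable out of a randomised comparison is legitimate, covariates are commonly settled in a statistical analysis plan, and a journal article condenses its protocol. This stands, and it is why the point is only an improvement. It does not dispose of the point, because the article does fix the model: its factors, its time points and its post hoc test.

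A second objection is that the gain may not reach the treatment effect, since a stable age effect cancels from change from baseline. This also stands, and it limits the claim to comparisons of CPM means between arms. The section does not say which contrast or error term the Tukey comparisons will use.

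Four stronger readings are tempting, and the documents do not support them.
- *Chance age differences between arms bias the result.* Randomisation keeps the comparison unbiased, and the unadjusted standard error already covers such gaps (step 4). The section also plans a per-protocol analysis of the primary outcome, where age gaps need not be due to chance alone, but nothing in the documents links age to dropout or adherence.
- *The protocol asserts that CPM declines with age.* It reports only that one study hinted at this.
- *The protocol claims that the entry limit removes the age effect.* It does not, so Study strengths needs no rewording.
- *Age is handled nowhere but at entry.* That is true of the randomised comparison only. Age also enters the baseline comparison and the correlation analysis with CPM, and may enter the responder regression.

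**Conclusion.** The point holds as a minor matter of efficiency. The plan collects a variable that it suspects is related to its primary outcome and does not use it in the randomised CPM comparison. The comparison stays valid, and the sample size and 87% power need no change.

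For age alone, and for CPM compared at one time point, power at 30 per arm would rise from 86.1% to 86.5% at r = 0.1 and to 91.4% at r = 0.4. This rests on an assumed correlation, and below about 0.3 the gain is under three percentage points. Little or no gain is expected for change-from-baseline contrasts if age affects only the level of CPM. Once baseline CPM is also in the model, the further gain from age may be smaller than the table shows, because baseline CPM would already carry part of any stable age effect.

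**What to change.** Prespecify baseline age, as a continuous covariate, together with baseline CPM, in the model that compares post-baseline CPM (3 and 6 months) between the four randomised arms. Baseline CPM then becomes a covariate and is no longer a level of the time factor. Take the pairwise comparisons between arms from this model as covariate-adjusted contrasts, with control for multiplicity.

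The cost is one degree of freedom for age and one for baseline CPM. Both are already collected, so recruitment, assessments and sample size do not change.

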### Study limitations

Limiting the study to CS-positive participants will limit the generalization of the results. Long-term effects of exercises on CPM will not be evaluated, and the results may not be applicable to the older population. The role of confounding factors such as gender, body mass index, and level of physical activities will not be considered in this study. Future studies should evaluate the role of potential confounders associated with the CPM response.

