### Objectives {7}

The primary objective of the present study is to determine if different exercise types produce varied outputs on CPM in a subgroup of CLBP patients classified as having CS pain. The secondary objectives are to evaluate if a 12-week exercise intervention program would alter executive functioning, QoL, disability, and pain and to examine the relationship between patient characteristics, executive functions, CPM, and QoL in CLBP patients.

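### The CPM, executive-function and QoL association is planned only as an unadjusted Pearson correlation, although age, gender and BMI are collected and could be adjusted for

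*Protocol article*

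**What the plan says.** Objectives {7} sets as a secondary aim "to examine the relationship between patient characteristics, executive functions, CPM, and QoL in CLBP patients".

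Statistical methods {20a,b} names the method: "Pearson correlation analysis will be performed to determine the relationship between patient characteristics (Table 4), CPM, executive functioning, pain, strength measures, disability, and QoL". Table 4, in the same section, lists age, gender and BMI for both the CLBP and the control group. It does not list level of physical activity. The one multivariable model in that section has another purpose: "Multiple linear regression analysis will be used to deduce the characteristics of individuals responding positively to exercise interventions".

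Study limitations states: "The role of confounding factors such as gender, body mass index, and level of physical activities will not be considered in this study". It continues: "Future studies should evaluate the role of potential confounders associated with the CPM response". Study strengths gives the reason for the 18 to 59 age limit: "a previous study has hinted at a decline in endogenous pain modulatory and CPM functions with advancing age".

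**The concern.** The association between CPM and executive function is observational, even though it sits inside a randomised trial. Random allocation balances the arms. It does nothing to separate two traits measured in the same person from a third factor that drives both. The protocol itself calls gender and BMI confounding factors and ties CPM to age. The executive-function measures are a timed colour-word task and a working-memory test. If any of the three factors also relates to those scores, a raw coefficient mixes that shared dependence with any direct link.

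At stake is how the result can be read. The Discussion wants the relationship between executive functions, CPM and QoL to feed later randomised trials. An unadjusted coefficient alone is a weak basis for that when the main candidate confounders are already in the data set.

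The wording is also uneven. One section relates gender and BMI to CPM through the Table 4 characteristics, and another says that their role as confounders is not considered. A reader has to work out how the two fit.

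**Working it through.** **Reading the text.** The method for the association is fixed as Pearson, which is pairwise and unadjusted. Adjustment is expressly declined for gender and BMI. The planned multiple regression concerns who responds to exercise, not CPM against executive function. So this is a stated choice, not a detail left to an unseen analysis plan.

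**Sample sizes.** Sample size {14} assumes a difference of 80 kPa, SD 100 kPa, 30 per group and two-sided alpha 0.05.
- Normal approximation: power = Φ(0.8 × √15 − 1.96) = Φ(1.138) = 0.873. The noncentral t with 58 df gives 0.861. The stated 87% reproduces.
- Dropout: 30 / 0.70 = 42.9, so 43 per group, and 4 × 43 = 172 patients. Completers as planned: 4 × 30 = 120.

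These figures serve a two-group t-test. The plan gives no figure for the correlation analysis, so there is none to reproduce there.

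**Illustration (the correlations are assumed; the documents give none).** Let one factor have correlation *a* with CPM and *b* with an executive-function score, with no link between the two given that factor. Then:
- Raw correlation: r = a × b.
- Test statistic on the Fisher scale: z = atanh(r) × √(n − 3).
- Chance of p<0.05: P(Z > 1.96 − z) + P(Z < −1.96 − z).

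The smallest significant |r| is 0.150 at n = 172 and 0.179 at n = 120. With a = b:

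| a = b | raw r | n = 172 | n = 120 |
|---|---|---|---|
| 0.2 | 0.04 | 8% | 7% |
| 0.3 | 0.09 | 22% | 16% |
| 0.4 | 0.16 | 55% | 42% |

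Worked line for a = b = 0.4 and n = 172: r = 0.16; atanh(0.16) = 0.1614; z = 0.1614 × √169 = 2.098; P(Z > −0.138) = 0.555. An unequal pair, a = 0.3 and b = 0.4, gives r = 0.12 and about 35% at n = 172 or 26% at n = 120.

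**What adjustment does.** The partial correlation is (r − ab) / √((1 − a²)(1 − b²)). With r = ab it is zero, so the adjusted estimate removes the part due to the measured factor.

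**What adjustment costs in precision.** With three covariates the Fisher-scale standard error at n = 172 goes from 1/√169 = 0.0769 to 1/√166 = 0.0776, about 1% wider.

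**The case against.** The strongest reply has four parts.

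- **No contradiction.** A reader might infer that the two sections give incompatible instructions. They do not have to. The limitation concerns these variables as confounders and most naturally means that no confounder adjustment will be made. A study can describe how gender or BMI correlates with CPM without adjusting for either. This stands: what remains is wording to reconcile.
- **No false positives.** A reader might take the percentages above as an inflated type I error against 5%. They are not. If a shared factor induces r = 0.12, the marginal correlation is truly 0.12, and the Pearson test is right to detect it. The objective asks for a relationship and does not claim a direct one. This stands too: the concern is interpretation, not test validity.
- **Importance.** Study strengths presents the association of executive functioning, CPM and exercises together as a major contribution. The third term may refer to exercise effects, which the randomised arms address. That sentence should not be read as a claim for the CPM and executive-function correlation alone.
- **Disclosure and design.** The limitation is stated openly, and the age range is restricted because of the age effect. Both help in part. Disclosure is a poor substitute for adjusting with data in hand, and 18 to 59 is still a wide span of age.

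The documents also do not say that gender or BMI relates to either executive-function test, which confounding would require. So confounding is possible here, not shown.

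**Conclusion.** The point holds as an improvement to a secondary, observational analysis. The plan fixes an unadjusted correlation and declines to consider confounders that it names and measures. The resulting coefficient cannot be read as a link between CPM and executive function, or QoL, that is independent of age, gender and BMI.

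Its size is unknown. The range of 8% to 55% at n = 172 rests wholly on assumed correlations of 0.2 to 0.4 with each variable, a single shared factor and no direct link. It shows how readily a wholly indirect association could appear significant and is not an estimate for this trial.

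A reader might also infer that the exercise comparison is compromised. It is not: randomisation protects the between-arm contrasts, and the sample-size calculation does not depend on this point.

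**What to change.** 1. In Statistical methods {20a,b}, state that the associations among CPM, executive functions and QoL will also be reported as partial correlations, or regression coefficients, adjusted for age, gender and BMI, beside the raw Pearson values.
2. In Study limitations, reword the sentence on confounders so that it applies only to level of physical activity, which Table 4 does not list. This also reconciles it with the planned correlations of gender and BMI with CPM.

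The cost is two sentences of text and a few lines of analysis. All three covariates are already collected, and the loss of precision is about 1%.
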